## Abstract

**Background:**

Major Depressive Disorder (MDD) is a leading cause of disability worldwide. Approximately one-third of patients with MDD do not respond to treatment, and often exhibit elevated inflammation biomarkers, which are associated with worse prognosis. Previous research has linked healthier dietary patterns, such as the Mediterranean Diet (MedDiet), with a lower risk of MDD and symptoms of depression, potentially due to their anti-inflammatory properties. The aim of this study is to evaluate the effectiveness of a nutritional counselling intervention promoting MedDiet to alleviate symptoms of depression in adults recently diagnosed with MDD and presenting with elevated inflammation biomarkers.

**Methods:**

This study is a randomized controlled trial (RCT) that will recruit adults from outpatient clinics, between the ages of 18 and 70 years who have been diagnosed with MDD and are currently receiving treatment with the first prescribed antidepressant, and who exhibit elevated inflammation biomarkers (interleukin-6 and/or C-reactive protein). The control group will receive treatment-as-usual (TAU) only. The primary outcome of the study will be the change in symptoms of depression, as measured by the Beck Depression Inventory 2 (BDI-II), after 12 weeks of intervention. Data analysis will follow an intention-to-treat approach. Secondary outcomes will include changes in inflammation biomarkers, quality of life, adherence to the MedDiet, and cost-effectiveness of nutritional counselling. All outcomes will be assessed at baseline, after the 12-week intervention, and at 6- and 12-months post-baseline.

**Discussion:**

This study will be the first RCT to evaluate the effect of a nutritional intervention with anti-inflammatory properties, as an adjuvant in the treatment of MDD, in individuals diagnosed with MDD and elevated inflammation biomarkers. The results of this study may contribute to the development of more effective and personalized interventions for MDD patients with elevated inflammation biomarkers.

## Background

Major Depressive Disorder (MDD) is a global leading cause of disability, according to data from the Global Burden of Disease (2019) [1, 2]. It is a chronic condition, typically first diagnosed between mid-adolescence and mid-40s, usually characterized by alternating episodes of depression and remission, although some patients exhibit a persisting unremitting course [3]. In the individual’s life, MDD is associated with different adversities, namely a higher risk of cardiovascular diseases, physical comorbidities as well as associated with a reduced quality of life [4, 5]. When treated, these episodes tend to resolve within three to six months [3]. A significant challenge in treating MDD is the subset of patients who do not respond adequately to conventional treatment approaches, such as pharmacotherapy and psychotherapy [3]. Up to 60% of patients show insufficient response to the first antidepressant prescribed, and approximately 30% will fail to respond to multiple antidepressants, even with second-line medication, ultimately being diagnosed with treatment-resistant depression (TRD) [2, 3, 6].

Patients with non or partial to treatment response often show evidence of inflammatory dysregulation, including elevated levels of biomarkers such as Interleukin 6 (IL-6) and C-Reactive Protein (CRP), suggesting the involvement of inflammation pathways in the pathophysiology of MDD and resistance to pharmacological treatment [2]. Elevated pro-inflammatory cytokines have been linked to dysregulation of the hypothalamic-pituitary-adrenal axis, alterations in neurotransmitters metabolism, and decreased neuroplasticity, as indicated by reduced brain-derived neurotrophic factor levels [2]. These mechanisms have been implicated in the pathophysiology of MDD and pro-inflammatory cytokines have been proposed as negative predictors of treatment response [6–8]. Although not all patients show elevated levels of inflammation biomarkers, there is evidence that inflammation may play a role in some cases of MDD [9].

This hypothesis is supported by the high incidence of depression in patients with infections and autoimmune diseases, undergoing cytokine therapy, as well as in patients with Hepatitis C and cancer treated with interferon-alpha, who often experience elevated levels of pro-inflammatory cytokines and depression-like symptoms meeting the diagnostic criteria for MDD. In most cases, depression symptoms and inflammatory cytokines decrease shortly after treatment ends [9, 10]. Additionally, in patients with elevated inflammation biomarkers, Non-Steroidal Anti-Inflammatory Drugs (NSAIDs) are effective in treating MDD, albeit with the typical side effects of this drug class [8, 11].

The role of diet in the incidence and prognosis of chronic diseases, such as cardiovascular disease, type 2 diabetes mellitus, and certain types of cancer, is well-established [12]. In recent years, the evidence linking nutrition and mental well-being has been growing [13]. Diseases that show improvement with nutritional interventions promoting healthier diets often have an inflammatory nature, and the literature attributes the health benefits of these diets to their anti-inflammatory properties [14].

Although the relationship between diet and MDD as not been has extensively studied as other chronic diseases, the available evidence compiled in meta-analysis of observational studies have found an association between healthier dietary patterns, including high intake of fruit, vegetables, fish, and whole grains, and a lower risk of depression, also experimental data reported meta-analysis of randomized controlled trials (RCTs) found that dietary interventions aimed at promoting healthier diets resulted in a reduction in symptoms of depression [15–17].

Diet may act via several pathways that are implicated in mental health, including pathways related to oxidative stress, gut microbiota dysbiosis, mitochondrial dysfunction, and inflammation [18].

The relationship between inflammation and depression suggests that a dietary intervention with anti-inflammatory properties may have a positive effect in reducing pro-inflammatory biomarkers [18]. As such, patients diagnosed with MDD who have elevated pro-inflammatory markers may have a better response to standard psychiatric treatment if they adopt dietary interventions with anti-inflammatory effects [19].

One dietary pattern that has been extensively studied is the Mediterranean Diet (MedDiet). Greater adherence to this diet is associated with a reduced risk of chronic diseases and overall mortality [20]. Studies evaluating the MedDiet have shown a decrease in pro-inflammatory biomarkers, with some authors attributing these to the diet’s anti-inflammatory properties [21].

While the anti-inflammatory potential of the MedDiet has also been identified in some of its nutrients and foods, such as omega-3 fatty acids, extra virgin olive oil, fish, fruit, vegetables, and whole grain intake, the overall effects of the MedDiet dietary pattern have shown better results in reducing inflammatory biomarkers than the summed effects of its components (e.g., through supplementation) [22, 23].

The effects of a modified version of the MedDiet, adjusted for the Australian population, on MDD treatment has already been studied in a Randomized Clinical Trial (RCT) by Jacka and colleagues, with positive results. About a third (32.3%) of the participants in the modified MedDiet group achieved remission from MDD compared to 8% in the control group, however conclusions from this study are limited by its small sample size [24].

Growing evidence suggests that the elevation of inflammation may be a potential determinant of resistance to conventional treatments for MDD. Despite this, there is a lack of evidence from controlled clinical trials assessing the potential effect of the MedDiet in treating patients suffering from MDD. To the best of our knowledge, this will be the first RCT to promote adherence to the MedDiet and screen patients for their inflammatory profile before the intervention, to assess its impact on MDD symptoms. The hypothesis being tested in this trial is that promoting adherence to the MedDiet as an adjuvant to standard treatments for MDD can reduce symptoms of depression in patients with MDD and elevated inflammation biomarkers (IL-6 and CRP).

## Methods/design

### Objectives

The main objective of the trial is to determine the effectiveness of nutritional counselling promoting the MedDiet as an adjuvant treatment for MDD in reducing symptoms of depression in adults diagnosed with MDD and elevated inflammation biomarkers (CRP, IL-6).

Other specific objectives of the trial are:

To test the association between adherence to the MedDiet and changes in CRP and IL-6.To test the association between changes in CRP and IL-6 and symptoms of depression.To test the association between adherence to the MedDiet and alterations in symptoms of depression.To identify the relationship between adherence to the MedDiet and changes in health-related quality of life.To evaluate the economic cost-effectiveness of dietary counselling as an adjuvant treatment for MDD.

### Clinical trial register

The present study is registered at ClinicalTrials.gov Protocol Registration and Results System (PRS) under the number: NCT05745194. Any modifications to the study’s protocol will be submitted to the trial’s register prior to implementation.

### Study design

This is a 12-week, multicentre, randomized, parallel-group, open-label controlled trial. Participants will be randomly assigned in a 1:1 ratio to either: (a) the intervention group, which will receive six nutritional appointments with a registered nutritionist promoting adherence to the MedDiet, in addition to the usual treatment for MDD, or (b) the control group, which will only receive the usual treatment for MDD.

Follow-up assessments will be conducted at 6 and 12 months after baseline assessment. More detailed information about the recruitment and allocation process is provided in Fig. 1.

This study protocol was developed by the Standard Protocol Items: Recommendations for Interventional Trials (SPIRIT) guidelines, and the results will be reported according to the Consolidated Standards of Reporting Trials (CONSORT) 2010 guidelines and their extension for non-pharmacologic treatments.

### Study participants, study setting and recruitment

The study will include adult (18–70 years old) outpatients diagnosed with MDD and having elevated levels of inflammation, as indicated by CRP ≥ 3 mg/L and/or IL-6 > 1.8pg/ml. The participants will be recruited from three Portuguese geographical areas: Lisbon, Loures/Odivelas, and Leiria, and will be recruited from hospitals and primary healthcare units. Three hospitals (Hospital de Santa Maria in Lisbon, Hospital Beatriz Ângelo in Loures, and Hospital de Santo André in Leiria) have already agreed to participate in the study, and two clusters of primary health care centres have expressed interest in collaborating. Additional recruitment health units are planned to be added during the trial.

Potential participants will be invited to enroll by their medical doctors at participating recruitment centres during regular medical appointments, including primary health care consultations and outpatient psychiatric consultations. After accepting the initial invitation, a researcher from the study team will provide a detailed explanation of the study and will obtain a signed informed consent from individuals who decide to participate. The collection of blood samples to measure the concentration of CRP and IL-6 will only take place after the informed consent is signed.

To be eligible for the trial, individuals must meet the following criteria:

#### Inclusion criteria

Aged between 18 and 70 years old;Able to understand and provide informed consent;Able to read and write;Have a diagnosis of MDD (according to the International Classification of Diseases Version 10 F32.0; F32.1; F32.2 criteria).Score on the Beck Depression Inventory-II scale (BDI-II) > 13;Elevated biomarkers of inflammation (CRP ≥ 3 mg/l or IL-6 > 1.8pg/ml) [25];Able to eat a MedDiet without impeditive physical limitations, allergies, or intolerances;Treated with the first antidepressant prescribed for at least 4 weeks [26].

#### Exclusion criteria

Diagnosis of autoimmune diseases, thyroid dysfunction, or cancer;Diagnosis of bipolar disorder, psychotic disorders, eating disorders or substance abuse disorders;Reporting an infection 2 weeks before the blood sample collection;Pregnancy or lactation;Glucocorticoid medication;Currently participating in another intervention targeting diet, physical exercise, or MDD treatment;

### Allocation and randomization

To ensure that the allocation of participants to the intervention and control arms is adequately done, a computer-generated list of random numbers will be used, stratified by centre, in variable blocks of sizes 2, 4, and 6. The treatment allocation will be concealed from the researchers and will be done using sequentially numbered, opaque, sealed envelopes. This will help prevent bias in the allocation process and ensure the validity of the study results. The researchers responsible for preparing the allocation sequence and the envelopes used in the randomization process will not have contact with the participants.

To maximize enrollment and retain participants, training and information about the trial will be provided to the medical doctors involved in recruitment through meetings, flyers, and emails. In addition, the consultations will be scheduled at times that are convenient for participants and will take place near their typical healthcare appointments. This will help minimize the burden of participation and promote retention to the study.

### Sample size

Considering a two-sided significance level of 5% and a power of 80% and using data from the trial published by Jacka et al. [24], the minimum sample size required to detect a difference of 20% points in the proportions of participants with a decrease in the severity of depressive symptoms, between control and intervention groups (8 and 28%, respectively), after 12 weeks, is 114 participants (57 per arm). Such difference corresponds to an odds ratio of 4.5, considered clinically relevant and smaller than the effect size derived from the SMILES trial [24]. Taking into consideration an attrition of 40% at the end of the intervention, the minimum sample size estimated is 190 (95 per arm). Estimating a prevalence of elevated inflammation in 30% of MDD patients and 10% of patients that don’t meet other inclusion criteria, the number of recruited participants estimated is 700 [2, 9].

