## Data collection and outcomes

### Main outcome: symptoms of depression

Symptoms of depression will be assessed with the self-administered Beck Depression Inventory-II (BDI-II) [28] scale, which is a 21 item self-report instrument for measuring the severity of depression in adults and adolescents. The total score is the sum of scores on the 21 items, ranging from 0 to 63. The adequate validity and reliability of this measure [29, 30] and its ability assessing depressive symptoms and monitoring the efficacy of treatment [30] makes it a valuable instrument for the current study. The Portuguese version of the BDI-II [30] will be administered. This version presents adequate internal consistency and convergent validity.

To measure changes in the main outcome, the score of the BDI-II will be used categorically, considering the cut-offs proposed by Beck et al. (1996) 0–13 minimal depression; 14–19 mild depression; 20–28 moderate depression; 29–63 severe depression [31].

The success measure will be a decrease in category in the severity of depressive symptoms.

The analysis of the score of the BDI-II will also be performed using the scale score as a continuous variable.

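### The 8% control rate behind the sample size is the cited trial's remission rate, not a rate for a one-category BDI-II decrease, so the 80% power stated for a 20-point difference is unsupported for the endpoint analysed

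*Protocol article*

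**What the plan says.** - **Sample size.** With a two-sided 5% level, 80% power and data from the earlier modified-MedDiet trial, the section gives the number needed to detect a 20-point gap in the proportion showing "a decrease in the severity of depressive symptoms, between control and intervention groups (8 and 28%, respectively), after 12 weeks, is 114 participants", that is, 57 per arm. It adds: "Such difference corresponds to an odds ratio of 4.5". It calls this clinically relevant and smaller than the effect in the earlier trial. An allowance for 40% attrition raises the total to 190 (95 per arm).
- **Background.** For the same earlier trial, 32.3% of the "participants in the modified MedDiet group achieved remission from MDD compared to 8% in the control group".
- **Main outcome: symptoms of depression.** "The success measure will be a decrease in category in the severity of depressive symptoms". The BDI-II categories are 0–13, 14–19, 20–28 and 29–63. The Statistical analysis section compares the proportion with such a decrease between the arms as the main outcome.
- **Inclusion criteria.** BDI-II above 13, and at least 4 weeks on the first antidepressant prescribed.

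**The concern.** The control proportion used for sizing and the endpoint to be analysed are different quantities. The only 8% that the article reports from the cited trial is a remission rate. The stated odds ratios fit that reading: 32.3% versus 8% gives about 5.5, and the planned 4.5 is described as smaller than the earlier effect. Nowhere does the article give or defend 8% as the usual-care rate of a one-category BDI-II decrease.

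This matters because a fixed 20-point difference is easiest to detect when the control rate is near 0% or the intervention rate is near 100%. If the usual-care rate is above 8%, the binomial variance is larger and 57 per arm gives less than the stated power. A null result could then be read as coming from a trial with 80% power for 20 points when it had less.

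**Working it through.** **1. Inputs.** From Sample size: two-sided 5%, 80% power, 8% versus 28%, 57 analysed per arm, 40% attrition. From Study design: 1:1 allocation. The control rates in step 4 are assumptions, because the article gives none for this endpoint.

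**2. Reproducing the plan.** The pooled-variance formula for two proportions, with p̄ the mean of p₁ and p₂, is

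n per arm = [1.960·√(2p̄(1−p̄)) + 0.842·√(p₁(1−p₁)+p₂(1−p₂))]² / (p₁−p₂)²

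With p₁ = 0.08, p₂ = 0.28 and p̄ = 0.18: (1.065 + 0.442)² / 0.04 = 56.7, so 57 per arm, with power 80.2%. The odds ratio is (0.28/0.72)/(0.08/0.92) = 4.47. Attrition: 57/0.6 = 95 per arm, 190 in total. The plan's arithmetic is correct; the question is the input.

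**3. Direction of the mismatch.** Everyone enters above 13.
- *Mild starters (14–19)* succeed only by reaching 0–13, which is close to remission.
- *Moderate starters (20–28)* succeed at 19 or below, and *severe starters (29–63)* at 28 or below. Both can succeed without coming near remission.

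Unless nearly all participants start mild, the endpoint is easier than remission, so a usual-care rate above 8% is probable. The baseline severity mix is not stated.

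**4. Power for 20 points with 57 per arm.**

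Power = Φ{[0.20·√57 − 1.960·√(2p̄(1−p̄))] / √(p₁(1−p₁)+p₂(1−p₂))}

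Example at 30% versus 50%: (1.510 − 1.358)/0.678 = 0.224, and Φ(0.224) = 58.9%.

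| Control rate | Power for +20 points, 57 per arm | Difference detectable with 80% power | Analysed per arm for 80% power at +20 points |
|---|---|---|---|
| 8% (plan) | 80% | 20 points | 57 |
| 10% | 77% | 21 | 62 |
| 15% | 70% | 23 | 73 |
| 20% | 65% | 24 | 82 |
| 25% | 61% | 25 | 89 |
| 30% | 59% | 26 | 93 |
| 40% | 57% | 26 | 97 |
| 50% | 59% | 25 | 93 |

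The formula is symmetric, so 72% versus 92% behaves like 8% versus 28%. Power for 20 points is below 80% at every control rate between 8% and about 72%.

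**5. Holding the odds ratio at 4.5 instead.** At a 30% control rate the intervention odds are 4.5 × 0.30/0.70 = 1.93, which is 66% success and a 36-point difference. Power is then 98%, and it stays at 80% or more up to a control rate of about 72%. The odds ratio of 4.5 and the 20-point difference therefore describe the same effect only near 8% (or its mirror image near 72%).

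**The case against.** Several points on the other side carry weight.

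- **How high the control rate is.** A reader might infer a usual-care success rate of 40% or more from the Background, where "Up to 60% of patients show insufficient response to the first antidepressant prescribed", and from its statement that treated episodes tend to resolve in three to six months. The article does not support that step. Those are general figures for treated patients. This trial enrols people still above 13 after at least 4 weeks of treatment and with raised CRP or IL-6, and the Conclusion describes them as having a lower remission rate with usual treatments. The cited trial's definition of remission is not given either. So the direction is well supported, but no particular rate is, and at 10–15% the loss is modest.
- **Odds ratio.** The effect is also stated as an odds ratio of 4.5, and at that ratio power does not fall until the control rate passes about 72%. This stands as a limit on the point. But the section says the trial is sized to detect 20 points and gives the odds ratio only as what that difference corresponds to.
- **Attrition allowance.** With no attrition, 95 per arm would give about 79% power or more for 20 points at any control rate. The plan itself, however, budgets 95 in order to retain 57.
- **The 28%.** A reader might think the plan attributes 28% to the earlier trial. It does not; it presents the chosen difference as smaller than that trial's effect.
- **What is unaffected.** Type I error, the effect estimate and its confidence interval do not depend on this assumption.

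**Conclusion.** The point holds as a mismatch between the planning rate and the endpoint. The stated 80% power for 20 points is correct for 8% versus 28%, but the article reports that 8% as remission and analyses a different, generally easier endpoint. Under assumed control rates of 10% to 50%, power with 57 analysed per arm lies between 57% and 77%, and the detectable difference is about 21 to 26 points. The size of the loss depends on a usual-care rate that the article does not give. It also assumes that the 20-point absolute difference is the target and that attrition reaches the planned 40%.

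A reader might go further and conclude that the trial must be enlarged, or that the primary endpoint must change to the continuous BDI-II score. Neither follows. The article does not establish the control rate that would fix a new sample size, and analysis of the continuous score is already planned as secondary.

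**What to change.** In the Sample size section:

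1. Stop presenting the 8% remission rate as the control rate for a one-category BDI-II decrease.
2. State a usual-care rate or range for that endpoint at 12 weeks and justify it.
3. Restate, over that range, the power that 57 analysed per arm gives for 20 points, or the difference detectable with 80% power.
4. Say whether the 20-point difference or the odds ratio of 4.5 is the target, since away from 8% the two part company.

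The cost is a change of wording in the protocol, and in the registry entry if it repeats the figure. No extra patients and no change of primary endpoint are needed. The downside is a less favourable stated power or detectable difference.

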### Intervention

Participants randomly allocated to the intervention group will attend six nutrition appointments with a duration between 30 and 60 min, in one of the participating centres of the trial, performed by a registered nutritionist in weeks 1, 2, 4, 6, 8 and 10. The intervention will promote adherence to the MedDiet without specific recommendations for weight change or calorie intake control.

Registered nutritionists involved in the intervention will participate in the baseline assessment but not in data collection at 12 weeks or at any of the follow-up assessments.

Both groups will maintain the TAU for MDD.

This trial will use a passive control group, with no active intervention apart from TAU.

All participants will have to be medicated with an antidepressant at the beginning of the trial. Changes in pharmacotherapy, including medicines and/or dosages, and additional treatments provided to participants (e.g., psychotherapy) will be documented and taken into consideration during statistical analysis.

